## Abstract

**Background:**

Although many patients with facial paralysis have obtained benefits or completely recovered after acupuncture or electroacupuncture therapy, it is still difficult to list intuitive evidence besides evaluation using neurological function scales and a few electrophysiologic data. Hence, the aim of this study is to use more intuitive and reliable detection techniques such as facial nerve magnetic resonance imaging (MRI), nerve electromyography, and F waves to observe changes in the anatomic morphology of facial nerves and nerve conduction before and after applying acupuncture or electroacupuncture, and to verify their effectiveness by combining neurological function scales.

**Methods/Design:**

A total of 132 patients with Bell’s palsy (grades III and IV in the House-Brackmann [HB] Facial Nerve Grading System) will be randomly divided into electroacupuncture, manual acupuncture, non-acupuncture, and medicine control groups. All the patients will be given electroacupuncture treatment after the acute period, except for patients in the medicine control group. The acupuncture or electroacupuncture treatments will be performed every 2 days until the patients recover or withdraw from the study. The primary outcome is analysis based on facial nerve functional scales (HB scale and Sunnybrook facial grading system), and the secondary outcome is analysis based on MRI, nerve electromyography and F-wave detection. All the patients will undergo MRI within 3 days after Bell’s palsy onset for observation of the signal intensity and facial nerve swelling of the unaffected and affected sides. They will also undergo facial nerve electromyography and F-wave detection within 1 week after onset of Bell’s palsy. Nerve function will be evaluated using the HB scale and Sunnybrook facial grading system at each hospital visit for treatment until the end of the study. The MRI, nerve electromyography, and F-wave detection will be performed again at 1 month after the onset of Bell’s palsy.

**Trial registration:**

Chinese Clinical Trials Register identifier: ChiCTR-IPR-14005730. Registered on 23 December 2014.

## Background

Acupuncture therapy is widely used for the treatment of Bell’s palsy in China and throughout the world [1–4]; however, its effectiveness is still debatable because conclusions drawn from Cochrane reviews [5, 6] and meta-analyses [7, 8] do not support its clinical application, whereas clinical trials tend to prove its efficacy [9, 10]. Except for some defects in the protocol design and implementation, different manipulations among Chinese and foreign physicians, and the lack of powerful evidence of objective detection and assessment besides the neurological function scale, are very important reasons for the conflicting opinions.

The detectable pathological changes of peripheral facial paralysis (including Bell’s palsy) are facial nerve edema and bioelectric conduction disorders. The former can be detected and evaluated using magnetic resonance imaging (MRI) [11–15], the latter using more sensitive neural electrophysiological methods [16].

Treatments for Bell’s palsy should differ according to the stage of the disease [17], and the most important factor in treatment is not the kind of manipulation but when to initiate the intervention, with the goal being to start in the acute stage within 7 days of palsy onset [18–20]. Currently, electroacupuncture is widely used in the treatment of Bell’s palsy, although there is inadequate evidence-based support, especially for use in the acute stage. On the one hand, some clinical experiences have revealed that an early and appropriate electroacupuncture therapy shortens the disease course and improves the curative effect [9, 21]. On the other hand, there are beliefs that electroacupuncture stimulation is not appropriate for patients in the acute stage of Bell’s palsy and that it is more likely to aggravate facial nerve edema and bioelectric conduction disorders. Thus, the efficacy of electroacupuncture for treating Bell’s palsy starting from the acute stage is yet to be investigated.

The purpose of this study is to investigate the effects of electroacupuncture therapy starting from the acute stage of Bell’s palsy. Symptom improvements will be evaluated by using the internationally accepted House-Brackmann (HB) Facial Nerve Grading System and the Sunnybrook facial grading system. Changes in facial nerve edema and nerve conduction will be analyzed by using MRI and neural electrophysiology techniques. The aim of the study is to provide a more reliable scientific basis for evaluating the effectiveness of electroacupuncture therapy for Bell’s palsy by combining clinical symptoms with physiology and electrophysiology findings.

## Methods/Design

### Study design

The present study is a randomized controlled clinical study (see Fig. 1).

**Fig. 1 Fig1:**
[figure not shown]
Flowchart of the study. *ENoP* neural electrophysiological

### Ethics

The trial will be carried out in accordance with the Declaration of Helsinki. Written informed consent will be obtained from each participant. This study is approved by the Medical Ethics Committee Board of Baoshan Integrated Traditional Chinese Medicine and Western Medicine Hospital of Shanghai (2014XBN02).

### Patients

Both outpatients and inpatients in the departments of acupuncture, neurology, and gerontology of Baoshan Integrated Traditional Chinese Medicine and Western Medicine Hospital of Shanghai, China, are being selected for inclusion. Male and female patients ranging in age from 18 to 60 years old are being enrolled. All the patients are being randomized into group A (electroacupuncture in the acute stage), group B (manual acupuncture in the acute stage), group C (non-acupuncture in the acute stage), or group D (medicine control group).

### Sample size calculation

Count data of the parallel controlled trial (1:1) will be analyzed statistically using a two-sided superiority test where α = 0.05, power = 90 %. The formula used for calculation is as follows:$$ n=\frac{{\left({Z}_{1-a}+{Z}_{1-\upbeta}\right)}^2\times \left({\sigma}_1^2+{\sigma}_2^2\right)}{\delta^2} $$

It is assumed that the change in the standard deviation of the Sunnybrook facial grading system score before and after the treatment in the control group is 10 points and that that in the treatment group is 18 points. A change will be considered clinically significant if the change of Sunnybrook scale score before and after the treatment in the treatment group is 13 points higher than that in the control group. The estimated sample size is arrived at as follows:$$ n=\frac{{\left({Z}_{1-a}+{Z}_{1-\upbeta}\right)}^2\times \left({\sigma}_1^2+{\sigma}_2^2\right)}{\delta^2}=\frac{{\left(1.96+1.28\right)}^2\times \left({10}^2+{18}^2\right)}{13^2}\approx 26.33 $$

It is assumed that the change in the standard deviation of HB scale score before and after the treatment in the control group is 1 point and that that in the treatment group is 3 points. A change will be considered clinically significant if the change of HB scale score before and after the treatment in the treatment group is 2 points higher than that in the control group. The estimated sample size is arrived at as follows:$$ n=\frac{{\left({Z}_{1-a}+{Z}_{1-\upbeta}\right)}^2\times \left({\sigma}_1^2+{\sigma}_2^2\right)}{\delta^2}=\frac{{\left(1.96+1.28\right)}^2\times \left({1}^2+{3}^2\right)}{2^2}=26 $$

It is determined that there should be at least 27 patients in each group. The dropout rate is considered to be 20 %, and thus at least 33 patients should be enrolled in each group. Hence, a total of 132 patients are required to conduct this study.

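### A minimum of 27 per group, 20% dropout and 33 enrolled per group (132 in all) do not agree: 27 needs 34 per group (136). The gap is minor and power by the plan's formula stays at about 90%

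*Protocol article*

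**What the plan says.** The Sample size calculation section of the protocol article plans a "two-sided superiority test where α = 0.05, power = 90" per cent. It works through the same formula twice, once for the Sunnybrook score and once for the House-Brackmann (HB) score, and prints about 26.33 and 26 per group. For Sunnybrook, the standard deviation of the change "in the control group is 10 points and that that in the treatment group is 18 points", and the difference to detect is a change that "in the treatment group is 13 points higher than that in the control group".

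The section then takes three steps:

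- It decides that "there should be at least 27 patients in each group".
- It takes the dropout rate as 20%, "and thus at least 33 patients should be enrolled in each group".
- It concludes that "a total of 132 patients are required to conduct this study".

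The Abstract (Methods/Design) repeats the headline number: "A total of 132 patients". The article gives no formula for the dropout step and does not say whether that step starts from 26.33 or from 27.

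**The concern.** As written, the enrolment figure is derived from the minimum of 27. A minimum that has to survive a given loss is divided by the fraction retained, and 27 divided by 0.80 is more than 33. Run backwards, 33 enrolled with 20% lost falls short of 27. So the minimum, the dropout rate and the enrolment figure cannot all stand.

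What is at stake is whether the headline sample size follows from its own inputs. A reader who checks 132 against 27 and 20% will not reproduce it, and cannot tell whether the minimum, the dropout allowance or the enrolment figure is the one to rely on.

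**Working it through.** **Inputs**, all from the Sample size calculation section: two-sided α = 0.05 and 90% power (z values 1.96 and 1.28); Sunnybrook SDs 10 and 18, difference 13; HB SDs 1 and 3, difference 2; minimum 27 per group; dropout 20%; 33 enrolled per group; four groups.

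**1. The plan's base figures.** n = (1.96 + 1.28)² × (σ₁² + σ₂²)/δ², with (3.24)² = 10.4976.

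- Sunnybrook: 10.4976 × (100 + 324)/169 = 26.34 (printed as about 26.33).
- HB: 10.4976 × (1 + 9)/4 = 26.24 (printed as 26).

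Both reproduce apart from the last digit. Rounding the larger one up gives 27.

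**2. Dropout from the stated minimum.** 27/(1 − 0.20) = 33.75, so 34 per group and 4 × 34 = 136 in total.

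**3. What 33 per group gives.**

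- Expected number left at 20% loss: 33 × 0.80 = 26.4.
- Largest loss that still leaves 27: 1 − 27/33 = 18.2%.
- In whole patients, losing 6 of 33 leaves 27 and losing 7 leaves 26.

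**4. Routes by which 33 could arise.**

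- Dividing the unrounded figure: 26.33/0.80 = 32.9, so 33 and 132.
- Multiplying the rounded figure: 27 × 1.2 = 32.4, so 33 and 132.

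The first is a correct allowance for dropout and the second is not. The article does not say which was used.

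**5. Power by the plan's own formula.** Power = Φ(δ/√((σ₁² + σ₂²)/n) − 1.96). For Sunnybrook at n = 26.4: √(424/26.4) = 4.008; 13/4.008 − 1.96 = 1.284; Φ(1.284) = 0.900.

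| Patients per group | Sunnybrook | HB |
|---|---|---|
| 26 | 89.6% | 89.7% |
| 26.4 (33 enrolled, 20% lost) | 90.0% | 90.1% |
| 27 | 90.7% | 90.8% |
| 27.2 (34 enrolled, 20% lost) | 90.9% | 91.0% |

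**6. Size of the gap.** 34 − 33 = 1 per group; 136 − 132 = 4 in total; 4/132 = 3%.

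**The case against.** The best defence is that 33 and 132 follow exactly from a correct method. Divide the unrounded 26.33 by 0.80, round up once at the end, and the printed figures appear. Rounding only at the end is ordinary practice, and 26.4 is still above the 26.33 that defines 90% power. This stands as far as it goes: it is not established that the inflation was done wrongly. It does not remove the inconsistency, because the text first fixes 27 as the requirement and then draws 33 from it, and 33 misses 27 at the stated loss whichever route was taken.

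It is also fair to say that the article calls 33 a floor, that the Statistical analysis section plans intention-to-treat as well as per-protocol analysis, so the number analysed need not fall to the completers, and that the assumed SDs and dropout rate are round figures whose uncertainty is far larger than one patient. These points make the matter small; they do not reconcile the figures.

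Three stronger readings are tempting, and the document does not support them:

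- A reader might infer that 33 was obtained as 27 × 1.2. That is only one of the two routes in step 4.
- A reader might infer that the promised 90% power is lost at 20% dropout. By the plan's formula it is 90.0% (Sunnybrook) and 90.1% (HB) at the expected 26.4, and less than half a point under 90% at a whole 26. A Welch t-test calculation gives 88.1% for Sunnybrook at 26, but it already gives 89.3% at 27. More than half of the drop from 90.7% (the plan's formula at 27) therefore comes from replacing the normal approximation (90.7 − 89.3 = 1.4 points) and the rest from the one patient (89.3 − 88.1 = 1.2 points).
- A reader might point out that, if each patient has an independent 20% chance of dropping out, a group of 33 keeps 27 or more only 50% of the time. With 34 this rises only to 63%. Sizing on expected loss never guarantees the minimum, so this is not evidence of an error.

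**Conclusion.** The inconsistency is real and minor. A minimum of 27 with 20% loss needs 34 per group and 136 in total. The stated 33 and 132 leave an expected 26.4 per group and cover at most 18.2% loss. The shortfall is one patient per group, four in all, or 3%.

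The practical consequence is close to nil, since the plan's own formula still gives about 90% power. The conclusion is therefore that the sample-size statement does not close on its own inputs, and not that the trial is underpowered. It rests on reading the 27 as the number to be left after dropout, which is how the text runs, and on taking 20% as the expected fraction lost in each group.

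**What to change.** Any one of these makes the section consistent:

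- Keep 132 and say that 33 per group leaves 27 at up to 18% loss and about 26 at 20% loss, with power of about 90% by the plan's formula.
- Keep 132 and say that the dropout allowance was applied to the unrounded 26.33, so that 27 is not guaranteed at 20% loss. This is the right choice only if it is what was done.
- Change the figures to 34 per group and 136 in total, both under Sample size calculation and in the Abstract (Methods/Design).

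The first two cost one sentence and no patients. The third costs four more patients and two edits.

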### Inclusion criteria

Patients with Bell’s palsy who meet the following inclusion criteria will be enrolled in the study: unilateral facial paralysis; age between 18 and 60 years; Bell’s palsy onset within 2 days; HB scale score above grade III; normal superficial and deep sensations, muscle strength and muscle tension in limbs, with negative pathological signs; and absence of heart failure, abnormal liver function, and other severe complications of diabetes mellitus.

### Exclusion criteria

Patients meeting any of the following criteria will be excluded from the study: pregnancy or breastfeeding; woman of childbearing age who is unwilling to use contraceptives during the study period; patients who received medicine or acupuncture therapy in other hospitals before this study; diabetes course ≥5 years, grade 3 hypertension ≥3 years, and hyperlipidemia ≥3 years; history of malignant tumor, sexually transmitted disease, renal or hepatic disease, gastric or duodenal ulcer, glaucoma, acute otitis, ipsilateral chronic otitis, tuberculosis, immunodeficiency syndromes, recent head injury, psychiatric disease, infectious disease, or any other condition that puts the person at risk of being influenced by the study treatment or that may affect the completion of the study; and participation in other clinical trials within 3 months.

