### Acute stage

Patients in groups A and B will receive acupuncture therapy at the Cuanzhu (BL2), Yangbai (GB14), Sizhukong (TE23), Qianzheng, Yingxiang (LI20), Quanliao (SI18), Dicang (ST4), Hegu (LI4), and Taichong (LR3) points. The acupuncture points are identified according to the method of point location issued by the World Health Organization (WHO). The acupuncture needles will be inserted straightly or obliquely with a depth of 10–30 mm to bring about the desired sensation of *deqi* (see Table 2), and the needles will be left in place for 20 minutes. The acupuncture therapy will be performed once every 2 days. Accordingly, patients in group A (electroacupuncture in the acute stage) will receive electroacupuncture therapy at the Yangbai (GB14)-Sizhukong (TE23), Quanliao (SI18)-Yingxiang (LI20), and Qianzheng-Dicang (ST4) points (2 Hz, density wave, 20 minutes) once every 2 days. Patients in group C will not receive acupuncture therapy.

**Table 2 Tab2:** Acupuncture points and needle insertion procedures

Acupuncture point	Direction	Depth (mm)
GB14 (yangbai, affected side)	Transversely toward geisoma	20–30
SJ23 (sizhukong, affected side)	Obliquely toward partes temporalis	20–30
Qianzheng (extra point, affected side)	Perpendicular to the skin	20–30
LI20 (yingxiang, affected side)	Obliquely along nasolabial sulcus toward the root of the nose	20–30
SI18 (quanliao, affected side)	Perpendicular to the skin	20–30
ST4 (dicang, affected side)	Transversely toward ST6	10–20
LI4 (hegu, bilateral)	Perpendicular to the skin	20–30
LR3 (taichong, bilateral)	Perpendicular to the skin	20–30

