### Western medicine treatment

Patients in each group will be given oral administration of prednisone (30 mg once daily for 5 days and then 5 mg daily until study withdrawal), mecobalamin (0.5 mg thrice daily), and fursutiamine (50 mg thrice daily) until complete recovery. Group D serves as the medicine control group, which will not be given any acupuncture or electroacupuncture therapy throughout the trial.

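### The prior-treatment exclusion depends on where treatment was given, so patients already treated for this palsy in the recruiting hospital, or by themselves, remain eligible

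*Protocol article*

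**What the plan says.** The Exclusion criteria in the protocol article remove "patients who received medicine or acupuncture therapy in other hospitals before this study". The Patients section recruits "Both outpatients and inpatients in the departments of acupuncture, neurology, and gerontology" of a single hospital, which is also the trial hospital. The Inclusion criteria require "Bell’s palsy onset within 2 days".

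Two arms are defined by the absence of acupuncture. For the acute stage, "Patients in group C will not receive acupuncture therapy". Group D is the medicine control, "which will not be given any acupuncture or electroacupuncture therapy throughout the trial" (Western medicine treatment). Drug treatment is common to all arms: "Patients in each group will be given oral administration of prednisone", together with mecobalamin and fursutiamine.

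The Primary outcome section records the two facial scales, the first change in score after treatment starts, and the interval from onset to that first change. The Statistical analysis section compares score changes from baseline.

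**The concern.** The sponsor evidently meant to keep out patients already treated, but the rule asks where they were treated. Acupuncture or a steroid given yesterday has the same consequence for the trial whether another hospital or the trial hospital's own acupuncture or neurology clinic gave it. Those clinics are where the trial finds its patients, so in-house treatment before enrolment is a realistic route.

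Two things are at stake. First, a patient who had acupuncture before enrolment can be randomised to an arm defined by having none (C in the acute stage, D throughout), which can shrink the contrast the trial is built to estimate. Second, for any pre-treated patient the baseline scores are not pre-treatment scores, the start of treatment is ambiguous, and an early change in score may have happened before anyone in the trial could record it.

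**Working it through.** **1. Is the gap real?** I read the Inclusion, Exclusion and Elimination criteria for anything else that would catch in-house or self-treatment.
- The Inclusion criteria set laterality, age, time since onset, severity, neurological status and comorbidity. None concerns prior treatment.
- The catch-all in the Exclusion criteria covers other conditions that put the patient at risk or may affect completion. It is about conditions, not earlier treatment.
- The Elimination criteria cover intracranial disease, consent and cooperation with randomisation.
- The statements that C and D receive no acupuncture govern treatment in the trial, not what came before it.

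So no stated criterion closes the gap.

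**2. How much acupuncture separates the arms?** Inputs: onset at most 2 days before entry (Inclusion criteria); "The acupuncture therapy will be performed once every 2 days" (Acute stage); A to C on the same electroacupuncture from the eighth day after onset (Stable and recovery stages). Assumption: the first session falls on the day of enrolment.
- Enrolled on day 0: sessions on days 0, 2, 4, 6 = 4.
- Enrolled on day 1: days 1, 3, 5, 7 = 4.
- Enrolled on day 2: days 2, 4, 6 = 3.

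The acute-stage contrast of A or B with C is therefore 3–4 sessions. The entry window leaves room for about one earlier session, which is 1/4 to 1/3, or 25–33%, of that contrast. This is a share per affected patient, and only for A or B against C. Against D, with the 12 sessions of Table 1, one session is 1/12, about 8%.

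**3. What could this do to power?** Reproduce the article's Sunnybrook calculation first:

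n = (1.96 + 1.28)² × (10² + 18²) / 13² = 10.4976 × 424 / 169 = 26.34, rounded up to 27 per group (the article gives 26.33 and 27).

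At n = 27, the standard error of the difference is √(424/27) = 3.963, and power = Φ(13/3.963 − 1.96) = Φ(1.32) = 0.907.

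Now let f be the share of patients pre-treated and r the net share of the effect each of them loses from the contrast. The expected difference becomes 13 × (1 − f·r). The documents give neither f nor r, so both are assumptions.

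| f | r = 0.25: difference, power | r = 1: difference, power |
|---|---|---|
| 5% | 12.84, 0.900 | 12.35, 0.876 |
| 10% | 12.67, 0.892 | 11.70, 0.840 |
| 20% | 12.35, 0.876 | 10.40, 0.747 |
| 30% | 12.03, 0.859 | 9.10, 0.632 |

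The r = 1 column is an outer bound. It would mean that about one session supplies the whole acute-stage effect, which is implausible.

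**4. Baseline and timing.** No arithmetic applies. The onset-to-first-change interval runs from a fixed origin, but a change before enrolment goes unseen. The first change after the start of treatment has no clear origin when treatment began before the trial.

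**The case against.** The strongest reply is randomisation. Prior treatment happens before allocation, so it is balanced in expectation over all four arms. If an A patient and a C patient each had one earlier session, the difference in their session counts is unchanged. On a strictly additive effect per session, r above is zero and nothing is diluted. Dilution needs the first session to count for more in a patient who would otherwise have none than in one who is about to have a full course. That is plausible but not shown, so the claim can only be that dilution may occur. What randomisation does settle is that there is no systematic bias between arms.

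A reader might infer that prior steroid contaminates the non-acupuncture arms. The documents do not support that: prednisone is background treatment in every group, so it is not part of the contrast. It affects only the baseline scores and the timing, in all arms alike.

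A reader might also infer that contamination has occurred, or in some stated number of patients. The article gives no count of pre-treated patients and no basis for estimating one.

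Nor should the criterion be read as barring anyone who ever took any medicine from another hospital. In a trial of palsy of at most 2 days' duration, the natural reading is treatment of this episode.

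Finally, the first electromyography, F-wave and (by the Secondary outcomes section) MRI measurements may be made up to 7 days after onset, so they may follow study treatment whatever this criterion says. That is a separate matter. It neither repairs nor worsens the gap for the primary scales.

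**Conclusion.** The point holds as a gap in a stated rule: read as written, it admits patients treated for the current palsy in the recruiting hospital or by themselves, and allows them into arms defined by having no acupuncture. The consequence is possible modest dilution of the acupuncture contrast, plus baseline scores and first-change times that do not start from an untreated state.

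The size is limited to about one session per affected patient. On the assumptions of 5–30% pre-treated and a quarter of the effect lost, power falls from 0.91 to between 0.90 and 0.86. This takes the 13-point difference to apply to the contrast affected; the article does not say which pair of arms it refers to. No stated sample-size figure changes. The reading of the criteria is certain; how many patients are affected is unknown.

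**What to change.** Reword the exclusion so that it turns on the treatment and not the place: any medicine, acupuncture or electroacupuncture given for the current episode of facial palsy before randomisation, from any source, including this hospital and self-treatment. Tying it to the current episode also removes any doubt about unrelated medicine.

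Recruitment began in January 2015, so some patients may have entered under the present wording. For them, record what was given before enrolment and when, and run a sensitivity analysis of the primary outcomes that excludes these patients or adjusts for prior treatment. Because prior treatment is fixed before randomisation, either approach leaves the randomised comparison intact.

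The cost is one sentence in the criteria, one item on the baseline form, and the loss of a few patients already treated in-house.
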